## Abstract

**Abstract:**

Ischaemic reperfusion (IR) injury is a major cause of graft loss, morbidity and mortality following orthotopic liver transplantation (OLT). Demand for liver transplantation has resulted in increasing use of marginal grafts that are more prone to IR injury. Remote ischaemic preconditioning (RIPC) reduces IR injury in experimental models, but recipient RIPC has not been evaluated clinically.

**Methods:**

A single-centre double-blind randomized controlled trial (RCT) is planned to test the hypothesis that recipient RIPC will reduce IR injury. RIPC will be performed following recipient anaesthetic induction but prior to skin incision. The protocol involves 3 cycles of 5 min of lower limb occlusion with a pneumatic tourniquet inflated to 200 mmHg alternating with 5 min of reperfusion. In the control group, the sham will involve the cuff being placed on the thigh but without being inflated.

The primary endpoint is ability to recruit patients to the trial and safety of RIPC. The key secondary endpoint is a reduction in serum aspartate transferase levels on the third post-operative day.

**Discussion:**

RIPC is a promising strategy to reduce IR injury in liver transplant recipients as there is a clear experimental basis, and the intervention is both inexpensive and easy to perform. This is the first trial to investigate RIPC in liver transplant recipients.

**Trial registration:**

Clinicaltrials.gov NCT00796588

**Electronic supplementary material:**

The online version of this article (doi:10.1186/s13737-016-0033-4) contains supplementary material, which is available to authorized users.

Ischaemia reperfusion (IR) injury, the injury which occurs when an organ’s blood supply is interrupted and reconstituted, is a major cause of morbidity and mortality post liver transplantation and is believed to account for at least 10 % of early graft loss [1]. Grafts from extended criteria donors are more prone to IR injury and the use of grafts from donors after cardiac death (DCD) is associated with a two-fold increase in risk of death and graft loss post transplantation in UK centres [2]. Due to a recent widening of the criteria for liver transplantation, there is greater demand for an already scare resource. In the UK, the use of grafts from DCD donors has increased from 6.9 % in 2005 [2] to 19.1 % of grafts implanted in 2013 [3]. There is no current accepted treatment of IR injury and as such strategies to ameliorate IR injury are of key clinical importance.

Ischaemic preconditioning (IPC), first described in 1986 in a canine cardiac model [4] has been shown to ameliorate warm hepatic IR injury in small animal models. Several small trials have been performed investigating the role of IPC of donor livers prior to retrieval [5–8]. The results are conflicting with only one trial demonstrating a better clinical outcome with fewer clinical episodes of clinical rejection in grafts from extended criteria donors following IPC [7], and two trials demonstrating a reduction in serum transaminases post transplantation [7, 8] with one trial reporting higher transaminase levels post transplantation following IPC [5]. No trial was able to demonstrate a reduction in graft loss or post-operative morbidity and mortality; however, none of the trials were powered to demonstrate a reduction in morbidity or mortality.

Paradoxically in small animal models, IPC has been shown to place added stress on the recovering liver impairing liver regeneration [9, 10], and in a multi-variate analysis of patients undergoing hepatic resection, IPC was found to be an independent risk factor for post-operative morbidity [11].

Remote ischaemic preconditioning (RIPC), first described in 1993 again in a canine cardiac model [12] has been found to provide protection against IR injury without adding stress to the target organ and as such is an attractive prospect for reducing IR injury in liver transplant recipients. Although RIPC has been shown to ameliorate hepatic IR injury in small animal models [13, 14], there has been no human liver transplant trial. Three recent trials have been performed in kidney transplantation including both living [15, 16] and deceased donors [17]. Two trials demonstrated evidence of an improvement in early graft function [15, 17]; however, one trial failed to demonstrate any evidence of improved graft function or reduced levels of biomarkers of graft injury [16]. Our aim is to perform a double-blinded randomized control trial to investigate the protection gained by RIPC in liver transplant recipients.

## Methods/design

### Study design and setting

RIPCOLT has been designed as a prospective double-blind randomized control trial with both surgeon and patient blinded to whether the recipient has received preconditioning. This protocol has been designed according to the SPIRIT guidelines [18]. The pilot will be carried out in a single centre—the Royal Free Hospital, London, with a subsequent multi-centre trial to establish cost effectiveness.

### Ethical approval

This trial has been approved by both the ethical board of the National Research Ethical Service (11/H0720/4) and the Royal Free Hospital/University College London ethical board (8191).

The trial has been registered with clinicaltrials.gov (NCT00796588).

### Participants

The pilot study will include 50 patients undergoing elective deceased donor liver transplantation at the Royal Free Hospital, London. Data will then be analysed regarding trial recruitment, completion of RIPC protocol, safety and preliminary evidence of efficacy to allow the endpoints and power of a subsequent multi-centre RCT to be designed. All patients undergoing deceased donor liver transplantation at the Royal Free Hospital will be considered for inclusion in the trial; exclusion criteria are contained in Table 1.

**Table 1 Tab1:** Exclusion criteria for trial

Exclusion criteria	Re-transplantation
	Patients under 16 years of age
	Super-urgent transplantation
	Lack of informed consent
	Combined liver and kidney transplantation
	Peripheral vascular disease
	Varicose veins
	Localized limb infection
	Prior history of thrombo-embolic disease
	Inclusion in another interventional trial

### Recruitment

Patients will be identified upon admission for transplant assessment and will be screened for inclusion and exclusion criteria. They will be provided with a patient information sheet and allowed 24 h to review the information prior to consenting by a member of the research team. A copy of the consent form and patient information sheet is included as an Additional file 1.

### Power calculation

A power calculation is not required for a pilot feasibility study [19]. However, guidance would suggest that 50 patients would be suitable for a feasibility study [20] with 25 randomized to receive RIPC and 25 to liver transplantation as per standard.

### Randomization

Participants are randomized to either the control or intervention group following induction of anaesthesia and collection of baseline blood samples. Randomization is performed via a random number sealed envelope system. Both the surgeon and the patient will be blinded to whether the patient receives RIPC.

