### Data analysis

Data will be stored on password-protected UCL computers in locked departments and will be anonymised prior to use. Since this is a feasibility study, all analyses other than recruitment rate and dropout rates should be considered exploratory. RIPC and control groups will be compared including both baseline characteristics and secondary outcomes. Continuous variables will be presented using means and standard deviations or medians and inter-quartile ranges, as appropriate, and binary variables will be presented as frequency counts and percentages. The mean difference in proportions (for binary outcomes) and the mean or median difference (for continuous outcomes) between the two groups will be explored and presented with 95 % confidence intervals.

This important data will be used to help the design of the multi-centre RCT.

Results will be analysed via Statistical Package for Social Sciences (SPSS) (IBM Chicago, IL, USA).

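### Envelope randomisation names no stratification by donor type, and the day-3 AST comparison is described as a crude difference: a minor, cheap improvement to an exploratory estimate

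*Protocol article*

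**What the plan says.** All places are in the protocol article.

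- **Randomization:** "Randomization is performed via a random number sealed envelope system". Allocation takes place after induction of anaesthesia and baseline blood sampling. No stratification factor is named.
- **Power calculation:** 50 patients, "25 randomized to receive RIPC and 25 to liver transplantation as per standard". No power calculation supports the number: "A power calculation is not required for a pilot feasibility study".
- **Introductory text after the abstract:** "Grafts from extended criteria donors are more prone to IR injury". The same paragraph links DCD grafts to a doubling of the risk of death and graft loss, and says their UK share rose from 6.9 % in 2005 to "19.1 % of grafts implanted in 2013".
- **Participants and Table 1:** every deceased donor recipient at the centre is considered, and DCD is not among the exclusions.
- **Data analysis:** "the mean or median difference (for continuous outcomes) between the two groups will be explored and presented with 95 % confidence intervals". No covariate is named. Everything except recruitment and dropout rates is labelled exploratory.
- **Abstract, Participants and Discussion:** day-3 AST is the key secondary endpoint, and the pilot's preliminary efficacy data are to inform the endpoints and power of the multi-centre trial.

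**The concern.** The protocol treats graft quality as prognostic for the injury that the trial tries to reduce, and day-3 AST is its main marker of early outcome. The Discussion also gives distortion of results in a small trial as a reason to exclude super-urgent recipients, and a similar reason for combined liver-kidney recipients. Nothing comparable is described for donor type, although DCD grafts may enter.

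At this size a handful of DCD grafts can fall unevenly. A crude AST difference would then contain a donor-type component that cannot be separated from a treatment effect. What is at stake is the quality of one exploratory estimate that feeds the design of the main trial. A covariate can be added later in an analysis plan. Stratification cannot, because it has to be settled before the envelopes are prepared.

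**Working it through.** The plan's figure of 50 comes from guidance. No alpha, power, effect or SD stands behind it, so there is no calculation to reproduce. The check instead sizes the consequence.

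**Inputs**
- From the protocol: 25 per arm; DCD share p = 0.191 (UK 2013) and 0.069 (UK 2005).
- Assumed: p = 0.30 as a high value, because the centre's own share is not given; DCD effect on AST d = 0.3 to 1.0 SD, with 1.5 SD as an extreme. The protocol gives no DCD effect on AST. One SD means the spread of AST within a donor type, on whatever scale it is analysed.

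**1. Chance imbalance.** Let the DCD counts in the two arms be independent Binomial(25, p).

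- Expected count per arm at p = 0.191: 25 × 0.191 = 4.8.
- SD of the between-arm difference: √(2 × 25 × 0.191 × 0.809) = √7.73 = 2.78.

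| p | Expected per arm | P(difference ≥ 3) | P(≥ 4) | P(≥ 5) |
|---|---|---|---|---|
| 0.069 | 1.7 | 0.16 | 0.05 | 0.01 |
| 0.191 | 4.8 | 0.37 | 0.21 | 0.10 |
| 0.30 (assumed) | 7.5 | 0.44 | 0.28 | 0.16 |

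If exactly 10 of the 50 grafts are DCD, the count in one arm is Hypergeometric(50, 10, 25), and a 7 v 3 split or worse has probability 0.29.

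**2. Shift in the crude AST difference.** Shift = (difference in DCD counts / 25) × d. For a difference of 4 this is 0.16 × d:

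- d = 0.3: 0.05 SD
- d = 0.5: 0.08 SD
- d = 1.0: 0.16 SD
- d = 1.5: 0.24 SD

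**3. Set against the precision.**

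- Standard error = √(2/25) = 0.283 SD.
- 95 % CI half-width = 1.96 × 0.283 = 0.55 SD.
- The shift is therefore 0.05/0.283 = 0.17 to 0.16/0.283 = 0.57 of a standard error for d = 0.3 to 1.0.
- The crude standard error also carries the donor-type variance. At d = 1.0 it is 0.283 × √(1 + 0.191 × 0.809 × 1.0²) = 0.283 × 1.074 = 0.304 SD, so the ratio falls to 0.16/0.304 = 0.53.
- For scale, the difference detectable with 80 % power at two-sided 5 % (both assumed) is (1.96 + 0.84) × 0.283 = 0.79 SD.

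**4. Gain from adjustment.** Share of variance due to donor type: R² = p(1 − p)d² / (1 + p(1 − p)d²). At p = 0.191:

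- d = 0.3: 0.0139/1.0139 = 0.014
- d = 1.0: 0.1545/1.1545 = 0.134

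The CI half-width is multiplied by √(1 − R²), which is 0.99 and 0.93.

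**The case against.** The case against is substantial.

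- **The design is legitimate.** An unstratified single-centre pilot of 50 is acceptable, and including DCD grafts is deliberate, because extended-criteria grafts motivate the trial. This stands: the point is an improvement, not an error or a contradiction.
- **No decision depends on it.** The primary endpoints are recruitment, feasibility and safety, and progression rests on consent of at least 60 % and dropout below 30 %. AST is exploratory, and the planned baseline comparison could reveal an imbalance. This stands and keeps the severity low.
- **Details may sit elsewhere.** Covariates are commonly left to an analysis plan, and envelope preparation to a full protocol; neither is shown. The missing covariate is therefore no finding on its own. Stratification is different only in timing, since an analysis plan cannot supply it afterwards. If the full protocol already stratifies, that half falls away.
- **The figures are conditional.** The centre's DCD share and the DCD effect on AST are not in the article. This stands, hence the ranges.

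A reader might also infer four stronger things that the text does not support:

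- *That the AST comparison is biased.* Unstratified randomisation is unbiased on average, and the crude CI already covers chance imbalance.
- *That the protocol names DCD as a principal cause of reperfusion injury.* It says only that extended-criteria grafts are more susceptible, and ties DCD to death and graft loss.
- *That the method cannot give 25 per arm.* That presumes simple randomisation. A fixed set of 50 shuffled envelopes fits the description equally well.
- *That leaving the choice of mean or median open is a fault.* That choice can be fixed in the analysis plan.

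**Conclusion.** The point holds as a minor design improvement. The article regards graft quality as prognostic and admits DCD grafts, yet it describes neither stratification nor adjustment by donor type. An imbalance of four or more DCD grafts has probability about 0.21 at a 19.1 % share, with 0.05 to 0.29 across the other scenarios examined. It would move the crude AST difference by 0.05 to 0.16 SD for an assumed DCD effect of 0.3 to 1.0 SD, and by 0.24 SD at 1.5 SD. Every one of these shifts lies well inside the 0.55 SD half-width. The issue is chance imbalance and a little lost precision in an estimate used for planning. The result rests on UK-wide DCD shares applied to one centre and on an assumed DCD effect.

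**What to change.** 1. Before recruitment, prepare two sets of sealed envelopes, one for DCD and one for other deceased donors, each in permuted blocks. Donor type should be known by the time of induction, but the article does not say that it reaches whoever opens the envelope, so state how it does.
2. Report the exploratory day-3 AST difference adjusted for donor type, with a 95 % CI, beside the crude difference.
3. If recruitment has begun, leave the allocation alone, make the adjustment and report donor type by arm.

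**Cost:** slightly more envelope handling and one degree of freedom. With blocks in two strata, the arms may end slightly off 25 v 25. **Gain:** the DCD count difference is held near zero or its effect on the estimate is removed, and the CI half-width shrinks by a factor of about 0.93 to 0.99 for the assumed effects of 1.0 to 0.3 SD. The sample size, primary endpoints and progression criteria do not change.

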### Trial protocol

Induction and maintenance of anaesthesia will be performed by intravenous propofol. The use of volatile inhaled induction agents such as sevoflurane have been shown to exert a degree of pharmacological preconditioning [21, 22] and as such they will be avoided.

Following induction but before the intervention, baseline blood and urine samples will be collected for measurement of pre-operative circulating cytokine levels and markers of renal parenchymal injury in both the blood and the urine.

A layer of stockinette will be applied to the left upper thigh with a wide pneumatic tourniquet applied over it in accordance with safe and recommended practices by the Association of Peri-operative Registered Nurses (AORN) [23] and Royal Free Hospital (RFH) departmental guidelines.

In those undergoing RIPC, the tourniquet will be inflated to 200 mmHg for 5 min followed by 5 min of reperfusion. This will be repeated three times.

In the control group, a sham will consist of the pneumatic tourniquet being placed on the left upper thigh without being inflated. The transplant will then proceed as standard.

Further blood samples will be collected 2 h following reperfusion of the graft to measure circulating cytokine levels post reperfusion. At the same time, two post reperfusion biopsies will be obtained. One of these biopsies will be fixed in 10 % natural buffered formalin for 48 h before being embedded in paraffin for H&E staining. IR injury will be graded by a pathologist according to the Suzuki classification of liver IR injury [24]. The second biopsy will be processed to extract fresh intra-hepatic lymphocytes for analysis by flow cytometry.

A further blood and urine sample will be obtained 24 h post reperfusion to measure circulating cytokine levels and markers of renal parenchymal injury both in the blood and urine.

All patients will receive standard post-operative care.

Routine clinical data will be collected including local complications as a result of RIPC, liver biochemistry, clotting profiles, urea and creatinine levels, post-operative complications, requirements for organ support, length of stay in the intensive care department and total hospital stay. Patients will be followed up for 3 months. A flow diagram of the trial is included in Fig. 1.

**Fig. 1 Fig1:**
[figure not shown]
Trial flow chart

### Outcome measures

The aim of this study is to assess the feasibility of recruiting liver transplant recipients and performing RIPC immediately prior to liver transplantations. The primary and secondary outcomes (Table 2) will help design a subsequent multi-centre RCT of RIPC in liver transplant recipients.

**Table 2 Tab2:** Primary and secondary endpoints

Primary endpoints	Ability to recruit patients to the trial
	Feasibility of performing RIPC in liver transplant recipients
	Safety of RIPC in liver transplant recipients
Secondary endpoints	AST levels on the third post-operative day [30]
	Incidence of acute kidney injury and need for renal replacement therapy
	Length of stay in intensive care and total hospital stay
	Incidence of vascular thrombotic events
	Incidence of biliary complications
	Incidence of post-operative infections
	Incidence of acute rejection in the first months post transplantation
	Circulating cytokine levels 2 h post reperfusion of the liver graft
	T cell accumulation and activation in the liver 2 h post reperfusion
	Urinary and serum NGAL levels 2 h post reperfusion

The criteria to progress to a full trial will be determined based on a consent rate of at least 60 % and post randomization dropout rate from the study of less than 30 %.

The safety of RIPC will be measured by incidence of localized complications following RIPC to include the development of a deep vein thrombosis or pulmonary embolus, the development of localized cellulitis and pain or paresthesia of the left lower limb following RIPC.

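### The primary safety endpoint is worded for the RIPC arm only, and the analysis section does not explicitly put it in the comparison with the sham arm

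*Protocol article*

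**What the plan says.** Table 2 of the protocol article (Outcome measures) lists "Safety of RIPC in liver transplant recipients" as a primary endpoint. The text below the table defines it: "The safety of RIPC will be measured by incidence of localized complications following RIPC". The events are deep vein thrombosis or pulmonary embolus, and then "the development of localized cellulitis and pain or paresthesia of the left lower limb following RIPC".

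The Trial protocol section describes collection: "Routine clinical data will be collected including local complications as a result of RIPC". The same section gives controls a matched device: "a sham will consist of the pneumatic tourniquet being placed on the left upper thigh without being inflated".

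The Data analysis section states: "RIPC and control groups will be compared including both baseline characteristics and secondary outcomes". It then says that differences in proportions for binary outcomes "between the two groups will be explored and presented with 95 % confidence intervals". It treats every analysis except recruitment and dropout as exploratory.

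**The concern.** Read as written, a control patient cannot have a safety event. The definition counts what follows RIPC, and the collection wording counts what RIPC caused. Controls have no RIPC, although they wear an uninflated cuff on the same thigh and so are the natural comparator.

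Two problems follow.

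- **Background.** None of the listed events is specific to a tourniquet. All can occur after major surgery, so a one-arm incidence is the sum of background and any cuff effect, and the two cannot be separated.
- **Attribution.** Recording an event as a result of RIPC needs a causal judgement, and that judgement is hard to make without knowing the allocation. It may lead to the same event being recorded in one arm and passed over in the other. This sits badly with a design that blinds surgeon and patient.

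The Discussion says the pilot data will be used to determine the safety of limb ischaemia in these patients. Few events could be read as safe, or background events as harm, without the sham rate beside them.

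**Working it through.** **Inputs.** Total 50, with 25 per arm (Power calculation section). The plan's only figure here is this total, and it reproduces: 25 + 25 = 50. The article gives no event rate, so the background rates below are assumptions shown as a range.

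**Step 1. What a one-arm count can say (n = 25).**
- 0 events, exact two-sided 95 % upper limit: 1 − 0.025^(1/25) = 0.137, or 13.7 %. The one-sided 95 % limit is 1 − 0.05^(1/25) = 0.113, or 11.3 %.
- 2 events: 2/25 = 8 %, exact (Clopper-Pearson) interval 1.0 % to 26.0 %.
- A true risk of 5 % gives no events with probability 0.95^25 = 0.277, about 28 %.

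**Step 2. What background alone would produce.** Suppose RIPC does no harm and the background risk is p. The expected count is 25p, and the chance of at least one event is 1 − (1 − p)^25.

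| Assumed p | Expected events in 25 | P(at least one) |
|---|---|---|
| 2 % | 0.5 | 40 % |
| 5 % | 1.25 | 72 % |
| 10 % | 2.5 | 93 % |
| 20 % | 5 | 99.6 % |

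The one-arm incidence overstates cuff harm by p, and nothing in that arm estimates p.

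**Step 3. What the two-arm comparison would give.** The interval is Newcombe's, which combines the Wilson limits of each arm. For 0/25 the Wilson upper limit is z²/(n + z²) = 3.84/28.84 = 0.133. For 0 v 0 the interval is therefore 0 ± 13.3 percentage points. A simple Wald interval would be 0 to 0, because both estimated variances are zero. Further illustrative counts (RIPC v sham):

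| Events | Difference (points) | 95 % interval |
|---|---|---|
| 2 v 2 | 0 | −17.9 to +17.9 |
| 3 v 1 | +8 | −9.4 to +26.3 |
| 5 v 2 | +12 | −8.3 to +32.0 |

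Power for a 10-point excess over backgrounds of 2, 5, 10 and 20 % is about 28, 21, 16 and 12 % (two-sided 5 %, normal approximation, rough at these counts). The comparison removes the background from the estimate. It does not make the estimate precise.

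**Step 4. What the secondary endpoints already cover.** Table 2 also lists vascular thrombotic events and post-operative infections, which are compared between arms.

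| Safety component | Secondary counterpart |
|---|---|
| Deep vein thrombosis, pulmonary embolus | Possibly vascular thrombotic events; inclusion not stated |
| Localized cellulitis | Possibly post-operative infections; inclusion not stated |
| Left lower limb pain or paraesthesia | None |

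**The case against.** The strongest reply is that the text does not exclude safety from the comparison. The analysis sentence says that the comparison includes baseline and secondary outcomes, which is not an exclusive list. The promise of a difference with a 95 % interval covers binary outcomes in general, and the safety events are binary. This stands: a reader might infer that safety was deliberately left out, but the article only fails to name it. It does not repair the definition, however. If events count only after RIPC, there is no valid control count to subtract.

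A reader might also infer that the sham arm is wasted, or that no excess harm can be estimated at all. Neither is supported. The sham serves the blinding, and the control group is the comparator for every secondary outcome. Thrombotic events and infections are compared between arms and may capture part of the safety set. Post-operative complications are collected as routine data.

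Three further points on the other side are fair.

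- The definition in Outcome measures is temporal, and its events could be recorded by blinded staff. Only the collection phrase is attributional, and the article does not say who assesses. One may not conclude that assessors are unblinded.
- No safety threshold enters the progression criteria, which concern consent (60 % or more) and dropout (under 30 %). A wrong safety reading would not by itself decide progression.
- The wide intervals mostly reflect a pilot size that the article openly leaves unpowered, and they remain wide after the fix.

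Finally, a reader might infer from the mixed background evidence on direct preconditioning that the safety set should be widened, for example to death and graft loss. That is a preference. The article reports conflicting transaminase results and a morbidity finding from liver resection patients, and it already lists several systemic complications as secondary endpoints.

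**Conclusion.** The point holds in a limited form. The primary safety endpoint is worded for RIPC recipients only, part of its collection rests on attribution, and its between-arm comparison is not explicit. Followed literally, it yields an incidence in 25 patients that mixes cuff harm with post-transplant background. No events would still allow a true risk of up to 13.7 %, and under assumed backgrounds of 2 to 20 % a harmless cuff would show at least one event with probability 40 to 99.6 %. The gap is clearest for limb pain and paraesthesia, which have no secondary counterpart. It is partial for thrombosis and cellulitis, because the overlap with secondary endpoints is possible but not stated.

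The conclusion assumes the literal reading of the definition and the collection text, and that the listed events occur at some rate without an inflated cuff. The full protocol is not shown and may record these events in all patients. The wording in the article should still be corrected, because it states a one-arm rule rather than merely leaving a detail out.

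**What to change.** Three changes of wording:

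1. **Outcome measures.** Define the listed events identically for all randomized patients, as occurring after cuff placement, inflated or sham.
2. **Trial protocol.** Replace the attributional phrase with recording of these events in every patient, without causal judgement and blind to allocation where possible. Patients are blinded, so limb pain and paraesthesia are well suited to this.
3. **Data analysis.** Name safety in the between-arm comparison as a RIPC-minus-sham risk difference, with a 95 % interval that remains valid for sparse counts (for example Newcombe). State that it is imprecise: with no events in either arm the interval is still about ±13 percentage points.

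The cost is the same case-report items for controls and a more modest safety claim. Sample size and intervention do not change. The change is best made before data collection, since limb symptoms never asked about in controls may not be recoverable later.
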